**Study rationale**

Human immunodeficiency virus (HIV)-related mortality has dropped significantly due to effective antiretroviral therapy. Epidemiological data suggest a less than 5% ten-year mortality for patients treated with anti-retroviral therapy (ART) (1). As a result of the reduction in early AIDS-related deaths, HIV has become a chronic disease manifesting the common components of chronic disease such as inflammation (2, 3), vascular dysfunction (4-6), and oxidative stress (7, 8). The combination of these adverse factors put HIV patients at increased risk of myocardial infarction (9) compared with age-matched subjects over the long term. A portion of this adverse cardiovascular risk has been linked to therapies necessary to survival in HIV. Several studies suggest that early protease inhibitors might increase the risk of myocardial infarction (10). The leading theory linking early PIs to myocardial infarction stemmed from the relationship between protease inhibitor use and the onset of an atherogenic dysmetabolism including the development of insulin resistance, dyslipidemia, and oxidative stress (11-14). With the advent of newer PIs, and the avoidance of certain NRTIs, the issue of lipodystrophy and insulin resistance has largely been resolved (15).

In contrast to the older protease inhibitors, atazanavir induces neither insulin resistance (16) or dyslipidemia (17). In addition, atazanavir has a property unique among protease inhibitors: elevation of unconjugated bilirubin by inhibiting the enzyme uridine diphosphate glucuronyltransferase (UGT) 1A1 (18). Bilirubin, thought to be solely a waste product, is a potent intracellular antioxidant and may provide a cardiovascular protective effect (19, 20). We have demonstrated that higher levels of bilirubin within the normal range are associated with reduced rates of stroke and peripheral artery disease (21, 22). Patients with Gilbert’s Syndrome (chronic elevations of bilirubin as a result of genetically reduced UGT 1A1) have a lower rate of myocardial infarction compared with age-matched controls (23).

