**Correlative Studies**

We will measure blood-based markers of oxidative stress (myeloperoxidase, malondialdehyde, and bilirubin), inflammation (high sensitivity C-reactive protein and tumor necrosis factor alpha receptor 2), and insulin resistance (fasting insulin and glucose). Each of these tests will be correlated with baseline and change in vascular function.

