**Data and Statistical Plan**

[figure not shown]
The primary endpoint of this study will be endothelium-dependent, flow-mediated vasodilation of the brachial conduit artery in subjects randomized to atazanavir compared with subjects continuing their current therapy. Nitroglycerin-mediated, endothelium independent vasodilation will be a secondary endpoint. The analysis begins with descriptive and graphical summaries of each outcome measure at pre-treatment, treatment at 7 days, and post treatment and difference from pre to post treatment. The assessment of the normality of each outcome will be performed by plotting the raw data and transformation will be applied if necessary. The primary analysis of between-subject effects will be assessed using student t tests. Sample size calculation: This protocol will be powered to detect a statistically significant difference in both resistance arteriole and conduit artery studies. We will enroll 60 subjects for the randomized portion of this protocol. Thirty subjects will receive atazanavir and 30 will continue to receive their baseline ART. Nitric oxide accounts for 50-60% of the increase in vasodilation to reactive hyperemia (31). It is anticipated that atazanavir will improve absolute endothelium-dependent vasodilation approximately 3% during flow mediated vasodilation. (Please see the table to see a range of power based on effect.)

Analysis of markers of bilirubin, oxidant stress, inflammation, and insulin sensitivity: As key secondary endpoints, the analysis begins with descriptive and graphical summaries of each outcome measure at pre treatment, post treatment and difference from pre to post treatment. The assessment of the normality of each outcome will be performed by plotting the raw data and transformation will be applied if necessary. The primary analysis of between-subject effect will be assessed using paired student t tests. A Bonferroni correction will be applied to account for multiple comparisons. The relationship between changes in secondary markers and changes in vascular function will be assessed using multivariate analysis of variance (MANOVA).

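### Holm's step-down procedure could replace Bonferroni for the key secondary markers at no cost in error control: an optional efficiency gain, not a correction of an error

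*Protocol*

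**What the plan says.** The Protocol's Data and Statistical Plan gives the blood markers the status of key secondary endpoints: "As key secondary endpoints, the analysis begins with descriptive and graphical summaries of each outcome measure at pre treatment, post treatment". The test is named next: "The primary analysis of between-subject effect will be assessed using paired student t tests". The multiplicity rule follows: "A Bonferroni correction will be applied to account for multiple comparisons". No number of comparisons and no alpha are given.

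The markers are listed under Correlative Studies. Three are for "oxidative stress (myeloperoxidase, malondialdehyde, and bilirubin"). The other four are for "inflammation (high sensitivity C-reactive protein and tumor necrosis factor alpha receptor 2), and insulin resistance (fasting insulin and glucose"). That makes seven by count.

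The Study rationale describes a direct action of atazanavir on one of the seven: "elevation of unconjugated bilirubin by inhibiting the enzyme uridine diphosphate glucuronyltransferase (UGT) 1A1".

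**The concern.** In its ordinary form, Bonferroni tests every marker at alpha divided by the family size, however many of the others are clearly positive. Bilirubin is one of the seven. The drug raises it directly, the Hypothesis predicts the rise, and patients with raised baseline bilirubin are excluded from the randomised trial. Its rejection is close to assured, yet its seventh of the alpha is never released to the other six.

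Those six carry most of the secondary objective on oxidative stress, inflammation and insulin resistance. Holm's procedure passes on the alpha of each rejected hypothesis under the same family-wise guarantee. At stake is some power for those six markers. The validity of the analysis and the primary endpoint are not affected.

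**Working it through.** **Inputs from the Protocol.** 30 subjects per arm (Data and Statistical Plan); FMD difference of 3-4% and SD of 4%, with stated power of 81-96% (Sample Size); seven markers (Correlative Studies).

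**Assumed.** Alpha 0.05 two-sided; family size m = 7; a two-sample t test with 58 degrees of freedom; standardised marker effects d of 0.5 or 0.75. The 0.75 is borrowed from FMD (3/4), because the Protocol gives no effect size or SD for any marker.

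**Step 1: the plan's own figure.** The Protocol says only that the trial is "powered to detect a statistically significant difference in both resistance arteriole and conduit artery studies", without an alpha. With two-sided 0.05, 30 per arm and the noncentral t distribution, power for FMD is 81.5% at a difference of 3% and 96.8% at 4%. This agrees with the stated 81-96% and supports the assumed alpha.

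**Step 2: thresholds.**
- Bonferroni: every marker at 0.05/7 = 0.00714.
- Holm: ordered p-values at 0.05/7, 0.05/6, ..., 0.05/1, that is 0.00714, 0.00833, 0.0100, 0.0125, 0.0167, 0.025 and 0.05, stopping at the first failure.

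The first threshold is the same under both. So the smallest p-value gains nothing, and the chance of at least one rejection is identical.

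**Step 3: power of one marker at each threshold** (noncentrality d × √(30/2); for d = 0.75 this is 0.75 × 3.873 = 2.90).

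| Threshold | d = 0.5 | d = 0.75 |
|---|---|---|
| 0.05/7 | 20.8% | 54.9% |
| 0.05/6 | 22.4% | 57.1% |
| 0.05/5 | 24.4% | 59.7% |
| 0.05/4 | 27.0% | 62.9% |
| 0.05/3 | 30.7% | 67.0% |
| 0.05/2 | 36.4% | 72.6% |
| 0.05/1 | 47.8% | 81.5% |

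Rejecting bilirubin alone moves the next threshold only from 0.05/7 to 0.05/6, which is worth about 2 points. Larger gains need further markers to be rejected as well.

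**Step 4: the whole procedure.** Seven t statistics were simulated 100,000 times per scenario, with bilirubin certain to be rejected (d = 3) and inter-marker correlation of 0, 0.3 or 0.6. Power is per responding marker other than bilirubin.

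| Responding markers besides bilirubin | Bonferroni | Holm |
|---|---|---|
| Two at 0.75 (myeloperoxidase, malondialdehyde) | 55% | about 59% |
| All six at 0.5 | 21% | 25-28% |
| All six at 0.75 | 55% | 68-70% |

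In no run did Bonferroni reject a marker that Holm did not.

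**Step 5: error control** (independent markers). With no true effects, the family-wise error is 0.048 under both methods. With an effect on bilirubin only, it is 0.042 under Bonferroni and 0.049 under Holm. With correlated markers it is lower. Holm uses more of the permitted 0.05 and does not exceed it.

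**The case against.** The strongest objection is that nothing here is wrong. A prespecified Bonferroni correction is valid, conservative and common for secondary endpoints. It contradicts nothing in the Protocol, biases no estimate and leaves FMD untouched. It also gives simple simultaneous confidence intervals. All of this stands, and it is why the point is only a suggestion.

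Three stronger readings might be inferred, and the Protocol supports none of them:

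- **That Bonferroni costs power on every marker.** It does not. The smallest p-value faces 0.05/7 under either method.
- **That the gain is the 13-15 points seen when all six others respond at 0.75.** The Protocol gives no marker effects, and its text points to a narrower response. The Hypothesis predicts higher bilirubin, less oxidative stress and better FMD, but does not mention inflammation or insulin resistance. The Study rationale regards insulin resistance as largely resolved with newer protease inhibitors. The scenario nearest the Hypothesis is two responding oxidative-stress markers, with a gain of about 4 points.
- **That the secondary objective is shown to be short of power.** No marker power is stated, and none can be derived without invented effects.

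Two further objections stand in part. The single-step form is the ordinary reading of the word Bonferroni, but the Protocol does not spell it out. And the power figures above come from an unpaired test, whereas the Protocol names a paired one for a between-subject effect. That wording is a separate matter to resolve; Holm's procedure works with p-values from any valid between-arm test.

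**Conclusion.** A cheap improvement, not an error. For testing the marker family, Holm's procedure is never worse than Bonferroni: it has the same strong family-wise control under any dependence, and at least the same rejections. That conclusion does not depend on the assumed effects.

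The size of the gain does. It is nil for the smallest p-value, about 4 points per marker if only the two other oxidative-stress markers respond at 0.75, 4-7 points if all six respond at 0.5, and 13-15 points if all six respond at 0.75. These figures rest on a family of seven, two-sided 0.05, 30 evaluable subjects per arm, a two-sample t test and a rejected bilirubin comparison. They illustrate the possible gain and do not predict it.

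**What to change.** Replace the Bonferroni sentence in the Data and Statistical Plan with:

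> The between-arm comparisons of the seven secondary markers will be adjusted by Holm's step-down procedure at a family-wise two-sided 0.05.

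This also states the family size and the alpha. It presumes that the p-values come from a test between the randomised arms, so the paired-test wording in the preceding sentence must be settled separately.

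The cost is one sentence, written before unblinded analysis, with no added patients, data or assumptions. The one drawback is that simultaneous confidence intervals are less direct than under Bonferroni. If unadjusted 95% intervals are shown beside Holm-adjusted p-values, they must be labelled as unadjusted, because an interval can exclude zero while the adjusted p-value exceeds 0.05.

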The benefit of atazanavir may be particularly important with the aging of the HIV population. More than 1/4^th^ of all patients with HIV are >50 years of age (24) and the sustained use of ART suggests that the aging of this population will continue, with 50% of the HIV population being older than 50 by 2015. Aging, per se, is an important cardiovascular risk factor and is associated with higher levels of oxidative stress (25-27) and endothelial dysfunction (28). It is plausible that use of atazanavir may improve vascular function through reductions in oxidative stress, ultimately reducing the rate of cardiovascular complications in patients with HIV. Accordingly, we hypothesize that the use of atazanavir in stable HIV patients over the age of 45 years will improve endothelial dysfunction and reduce oxidative stress compared with continuing the current therapy.

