**Sample Size**

It is estimated that the substitution of atazanavir and increase in bilirubin will increase endothelium-dependent, flow-mediated vasodilation FMD by 3-4%. With an estimated standard deviation of the measurement of 4% and a 1:1 randomization scheme, this yields a power of 81-96% with a sample size of 60 subjects in a parallel design trial.

For aim 2, we expect a similar difference in FMD to be noted between the 30 subjects on atazanavir and the 60 subjects at study entry for the primary aim, thus making the comparison 1:2, yielding a power range of 87-99% to detect a difference in flow-mediated vasodilation.

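### MANOVA is named to relate marker change to vascular change, which it does not estimate; a second section names correlation instead, and neither gives randomised arm a role

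*Protocol*

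**What the plan says.** Two places in the protocol address how marker changes relate to vascular changes.

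- **Data and Statistical Plan**, paragraph on bilirubin, oxidant stress, inflammation and insulin sensitivity: the link between marker change and vascular change "will be assessed using multivariate analysis of variance (MANOVA". No factor, outcome set or covariate is given.
- **Correlative Studies**, after the list of seven blood measures (myeloperoxidase, malondialdehyde, bilirubin, hsCRP, TNF-alpha receptor 2, insulin, glucose): "Each of these tests will be correlated with baseline and change in vascular function".

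Neither place says whether the arms are combined, analysed separately or adjusted for. The study rationale explains why the question is asked. It proposes that "use of atazanavir may improve vascular function through reductions in oxidative stress", and the Hypothesis section expects atazanavir to raise bilirubin, lower oxidative stress and improve FMD.

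**The concern.** The aim is an association: do subjects whose marker changes more also show a larger change in FMD? Both quantities are continuous. A MANOVA with arm as its factor answers a different question, namely whether the arms differ on a set of outcomes taken together. A significant result would say nothing about whether marker change tracks FMD change.

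The other method on offer, correlation, does address association, but its result depends on what is done with arm. The drug is expected to shift both variables. If arm is left out, those two shifts alone can produce a correlation, even when the two changes are unrelated among subjects on the same treatment. Such a correlation would look like support for the proposed mechanism while carrying no information beyond the two treatment effects. This is the only analysis in the protocol that links marker change to vascular change, so the mechanistic conclusion rests on it.

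**Working it through.** **Inputs from the protocol**

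- FMD effect, from Sample Size: atazanavir "will increase endothelium-dependent, flow-mediated vasodilation FMD by 3-4" percentage points.
- Spread, from Sample Size: "With an estimated standard deviation of the measurement of 4% and a 1:1 randomization scheme".
- Allocation, from Data and Statistical Plan: "Thirty subjects will receive atazanavir and 30 will continue to receive their baseline ART".

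**Assumptions**

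- The 4% SD applies to the change in FMD.
- Tests are two-sided at 0.05 (the protocol states no alpha).
- The drug shifts a marker's change by 0.5 to 3 within-arm SDs. The protocol gives a direction for this but no size.

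**Step 1: reproduce the stated power.** The protocol says "this yields a power of 81-96% with a sample size of 60 subjects in a parallel design trial". For a two-sample t test with 30 per arm, the noncentrality is δ / (4 × √(2/30)) = δ / 1.033.

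- δ = 3: noncentrality 2.90, power 81.5%.
- δ = 4: noncentrality 3.87, power 96.8%.

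This matches the stated range to within a point, so 3/4 = 0.75 SD and 4/4 = 1.0 SD are fair readings of the planned FMD effect.

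**Step 2: correlation produced by arm alone.** Let d1 be the FMD effect and d2 the marker effect, both in within-arm SDs, with 1:1 allocation and zero within-arm correlation. Across both arms the covariance is d1·d2/4 and the variances are 1 + d1²/4 and 1 + d2²/4, so

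r = (d1·d2/4) / √[(1 + d1²/4)(1 + d2²/4)].

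- Smallest case, d1 = 0.75 and d2 = 0.5: 0.09375 / √(1.1406 × 1.0625) = 0.085.
- Largest case, d1 = 1.0 and d2 = 3: 0.75 / √(1.25 × 3.25) = 0.372.

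For a marker that the drug lowers, the sign is negative and the size is the same.

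**Step 3: how often this would be significant.** Simulation of 10,000 trials of 30 + 30 for each case, with no within-arm association:

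| FMD effect (SD) | Marker effect (SD) | Expected r, arm omitted | Significant, arm omitted | Significant, arm included |
|---|---|---|---|---|
| 0 | 0.5 to 3 | 0 | 5% | 5% |
| 0.75 | 0.5 | 0.085 | 10% | 5% |
| 0.75 | 1 | 0.157 | 23% | 5% |
| 0.75 | 2 | 0.248 | 51% | 5–6% |
| 0.75 | 3 | 0.292 | 65% | 5% |
| 1.0 | 0.5 | 0.108 | 13% | 5% |
| 1.0 | 1 | 0.200 | 35% | 5% |
| 1.0 | 2 | 0.316 | 73% | 5% |
| 1.0 | 3 | 0.372 | 87% | 5% |

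The distortion is greatest for a marker that the drug moves strongly, as it is expected to do with bilirubin. It is small for a marker that the drug barely moves.

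**The case against.** **The protocol does not say the arms are pooled.** This is correct. A reader might infer from the Correlative Studies sentence that all subjects are correlated together and arm is ignored. The text is silent, and covariates for an explanatory analysis are often left to a statistical analysis plan, which is not at hand. Silence on arm would therefore not be a finding by itself. What remains is that the method which is stated does not fit its stated aim, and that two sections name different methods for one question.

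**MANOVA would naturally take arm as its factor, and its residual matrix holds arm-adjusted correlations.** Also correct. However, the MANOVA test neither reports nor tests those correlations, and the protocol does not say they will be extracted. If a multivariate linear model with marker change as a continuous predictor is what is meant, that is a regression and should be described as one.

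**The distortion may be modest.** One might infer that any drug effect on both variables must show up as a mechanistic link. The table does not support that: the rate is about 10% to 13% for a marker effect of 0.5 SD and falls to 5% if FMD does not move. The Bonferroni correction in the same paragraph might also extend to this analysis, though the text does not make that clear. With seven markers (0.05/7), an FMD effect of 0.75 SD and a marker effect of 2.5 SD (expected r 0.27), the rate falls from about 59% to about 29%. That reduces the problem without removing it.

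**Correlations with baseline vascular function are sound.** This stands in full. Baseline measures precede treatment, so randomised arm cannot confound associations among them.

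**Conclusion.** The point holds in a limited form. MANOVA, as written, does not estimate the relationship it is assigned to. Correlation is named elsewhere for the same purpose, and the role of arm is unstated in both places. If the change-versus-change correlation were run on all 60 subjects without arm, treatment effects alone would give an expected correlation of about 0.09 to 0.37, nominally significant in about 10% to 87% of trials, against about 5% with arm included.

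That range is conditional on the planned FMD benefit occurring, on the 4% SD applying to change, and on the assumed marker effects. It shows what the wording leaves open. It does not show that the trial will analyse its data this way. The primary FMD comparison and the between-arm marker comparisons are not touched by this point.

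**What to change.** In the Data and Statistical Plan, replace MANOVA with a linear regression of follow-up FMD on change in each marker, adjusted for baseline FMD, baseline marker value and randomised arm. Report the within-arm slope with its 95% confidence interval and label it exploratory. In Correlative Studies, use the same model for the correlations with change in vascular function, so that the two sections agree. Leave the correlations with baseline vascular function as they are.

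The change is to wording only and needs no new data. The cost is precision. Across both arms the marker variance is 1 + d2²/4 times the within-arm variance. For the same residual SD, the standard error of the slope therefore grows by √(1 + d2²/4): about 1.03 times at d2 = 0.5 and √3.25 ≈ 1.80 times at d2 = 3. For a marker that largely separates the arms, the interval will be wide, which fairly reflects how little 60 subjects can say about the within-arm link.

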**Secondary Objectives**

The secondary objective of this study is to determine whether switching to atazanavir reduces oxidative stress, inflammation, and insulin resistance compared with nonatazanavir ART.

In a second analysis, we will recruit 30 stable subjects on atazanavir for more than 6 months meeting the primary objective entry criteria, to perform a single vascular function and metabolic evaluation to determine if chronic atazanavir, when compared to nonatazanavir regimens has lower levels of oxidative stress and improved vascular endothelial function.

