**Key Inclusion Criteria**

- Age ≥ 45 years
- Stable non-atazanavir-containing regimen consisting of co-formulated tenofovir/emtricitabine as the NRTIs plus a third agent for 3 months or longer. The third agent can be any FDA-approved PI, NNRTI, or raltegravir.
- HIV RNA < 50 cop/mL at screening and at least once within the prior year,
- No treatment interruptions > 7 days in the 3 months prior to study entry

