**Key Exclusion Criteria**

- Prior treatment failure on or intolerance to atazanavir
- Known or suspected resistance to atazanavir
- Patients with Gilbert’s Syndrome or elevated bilirubin levels (> 1.5 mg/dL) at baseline (for the randomized trial)
- Receiving ART different from co-formulated tenofovir/emtricitabine plus third agent (PI, NNRTI, or raltegravir) regimen
- Current receipt of proton-pump inhibitor therapy
- Recent initiation of hormones or immunomodulators

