For the second protocol, vascular function for the 30 subjects stable on atazanavir will be compared to the baseline vascular function of the 60 subjects enrolled for the randomized protocol. The analysis plan, including descriptive and graphical summaries, testing of normality with transformation as needed, and between subject t testing will be applied similarly as in randomized trial.

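### Aim 2 applies the randomised trial's unadjusted t test to a non-randomised comparison, so background differences such as age can be read as an effect of atazanavir

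*Protocol*

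**What the plan says.** Under Secondary Objectives the protocol states: "we will recruit 30 stable subjects on atazanavir for more than 6 months meeting the primary objective entry criteria". The purpose is "to determine if chronic atazanavir, when compared to nonatazanavir regimens has lower levels of oxidative stress and improved vascular endothelial function". Each of the 30 has a single evaluation.

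The Data and Statistical Plan says that their vascular function "will be compared to the baseline vascular function of the 60 subjects enrolled for the randomized protocol", and that "between subject t testing will be applied similarly as in randomized trial". For the randomised trial the test is given as: "The primary analysis of between-subject effects will be assessed using student t tests". No covariate, matching or restriction is named for Aim 2.

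Four places bear on who enters each group:

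- Key Inclusion Criteria require "Stable non-atazanavir-containing regimen consisting of co-formulated tenofovir/emtricitabine as the NRTIs plus a third agent for 3 months or longer".
- Key Exclusion Criteria list "Patients with Gilbert’s Syndrome or elevated bilirubin levels (> 1.5 mg/dL) at baseline (for the randomized trial", a limit that leaves the second cohort outside this exclusion.
- Trial Population describes the second cohort separately: aged 45 or older, on suppressive tenofovir/emtricitabine with atazanavir/ritonavir.
- Secondary Objectives, as quoted above, say that the 30 meet the primary entry criteria.

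**The concern.** In the randomised part, a t test is a fair comparison because chance decides who receives atazanavir. In Aim 2, past prescribing and continued use decide it. The comparison uses values taken at trial entry, so the later randomisation of the 60 does nothing to balance them against the 30. The t test then estimates the drug difference plus whatever the groups' other differences contribute.

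The protocol supplies one such factor itself: the Study rationale says that ageing goes with more oxidative stress and with endothelial dysfunction. Both groups must be at least 45, but nothing makes their age distributions alike above that limit.

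What is at stake is the reading of a secondary result. The objective speaks of improved endothelial function, and a significant unadjusted difference would naturally be reported in those words.

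**Working it through.** **Inputs.** Group sizes of 30 and 60, SD of 4 and an expected difference of 3 to 4 points come from Sample Size. The protocol states no alpha, so two-sided 0.05 is assumed.

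**The plan's own figure.** The standard error is 4 × √(1/30 + 1/60) = 4 × √0.05 = 0.894, with 88 degrees of freedom. The noncentral t distribution gives power of 91.3% at 3 points and 99.3% at 4 points. The protocol states 87-99%: the upper end reproduces and the lower end does not. The same method with 30 vs 30 gives 81.5% and 96.8%, in line with the stated 81-96% for the primary aim. The 87% errs on the cautious side and is a separate, minor matter. Power has no bearing on bias.

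**Smallest significant difference.** With the observed SD at 4, the t test is significant once the observed difference exceeds t(0.975, 88) × 0.894 = about 1.78 points, which is well below the 3 to 4 points expected.

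**False-positive rate under confounding.** Suppose the drug has no effect and background factors shift the mean difference by b. For one linear factor, b is its slope on FMD times the difference in its mean between the groups. The protocol gives neither quantity, so every b below is an assumption. The noncentrality is b / 0.894.

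| Assumed b (FMD points) | Noncentrality | Probability of p<0.05 |
|---|---|---|
| 0 | 0 | 5.0% |
| 0.5 | 0.56 | 8.6% |
| 1.0 | 1.12 | 19.8% |
| 1.5 | 1.68 | 38.2% |
| 2.0 | 2.24 | 59.9% |

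**Is adjustment affordable?** Take five covariates (83 degrees of freedom) that explain a share R²y of FMD variance and a share R²g of group membership. The noncentrality for a true difference d is d × √(1 − R²g) / (0.894 × √(1 − R²y)). With R²y assumed between 0 and 0.3 and R²g between 0 and 0.2, power is 84-98% at d = 3 and 98-100% at d = 4. The least favourable case (R²y = 0, R²g = 0.2) has noncentrality 3 × 0.894 / 0.894 = 3.0 and power of 84.3%.

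**Entry rules side by side.**

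| Item | 60 comparators | 30 on atazanavir |
|---|---|---|
| Age | 45 or older | 45 or older |
| Time on regimen | 3 months or longer | more than 6 months |
| Third agent | any approved PI other than atazanavir, NNRTI or raltegravir | atazanavir/ritonavir |
| Gilbert's Syndrome | excluded | not excluded under Key Exclusion Criteria; excluded if Secondary Objectives are taken literally |
| Bilirubin above 1.5 mg/dL | excluded | same ambiguity |

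**The case against.** The strongest reply is that covariate lists and supporting analyses usually belong in an analysis plan, which is not shown here. That would answer a complaint about missing detail. However, the protocol does choose the method, by analogy with the randomised trial, and an adjusted main analysis would depart from it.

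The aim can also be read as a cross-sectional comparison, since it rests on one visit and asks what users of the drug have. That is fair. The word *improved* still invites a causal reading, so the wording deserves care.

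Several stronger readings are tempting, and the documents do not support them:

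- **That the 30 cannot qualify at all.** Read literally, the entry criteria demand a regimen without atazanavir. Trial Population, however, defines the second cohort separately, so the reference to the primary criteria is loose wording.
- **That the one-sided bilirubin cut-off is an error.** The Study rationale says that atazanavir raises bilirubin. A cut-off would remove the very people Aim 2 wants, so this asymmetry is unavoidable. Known Gilbert's Syndrome is a different question and is left open.
- **That the bias must favour atazanavir.** The protocol links Gilbert's Syndrome to fewer myocardial infarctions but says nothing of its effect on FMD or its frequency among atazanavir users. A favourable bias is plausible on the protocol's own reasoning but not shown.
- **That only the 30 are selected for tolerating their drug.** The comparators are also stable and suppressed, and may have been on their regimen far longer than the 3-month minimum. The 6-month and 3-month rules differ, but both groups are established users.
- **That the 1:2 split makes the pooled t test liberal.** With assumed SDs of 5 in the 30 and 3.5 in the 60, simulated type I error is about 8%. With the SDs reversed it is about 2.9%. The protocol gives no reason to expect either.

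**Conclusion.** The point holds for the method and the reading of Aim 2. The protocol fixes an unadjusted two-sample t test for a comparison without randomisation, while itself naming age as a correlate of the outcome. Followed as written, it can present confounding as a drug effect.

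The size is unknown. The rates of about 9% to 60% rest on assumed biases of 0.5 to 2 points, an SD of 4 and an assumed two-sided alpha of 0.05. They show how sensitive the test is and do not estimate the bias in this study. No imbalance in age or any other factor is documented.

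The statements of who may enter the atazanavir cohort need reconciling, but this is unclear wording and not proof of a biased sample. The matter is worth correcting and is limited to a secondary analysis.

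**What to change.** 1. Make the main Aim 2 analysis a linear regression of FMD, and of each blood marker compared in this aim, on group. Adjust for a short prespecified list of factors that the third agent does not affect: at least age and sex, plus smoking if it is recorded.
2. Keep lipids, diabetes and insulin resistance out of the main model. The Study rationale says that third agents differ in their metabolic effects, and insulin resistance is itself a study outcome. Adjusting for them could remove part of the difference sought, so they belong in a sensitivity analysis only.
3. Report the result as an association and reword the objective to match. Adjustment does not remove unmeasured confounding.
4. Reconcile Secondary Objectives with Trial Population and the Key Inclusion and Exclusion Criteria by stating which criteria apply to the atazanavir cohort, including how known Gilbert's Syndrome is handled.
5. If time on regimen is recorded, add a sensitivity analysis limited to comparators with more than 6 months on theirs.

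The cost is some protocol wording, a few degrees of freedom and a more modest claim. Under the ranges assumed above, power at a 3-point difference stays at 84% or more.
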